### Outcome measurements

2.13

#### Efficacy outcome

2.13.1

The primary outcome measure is the between-group difference in changes in MoCA-K scores 13 weeks after baseline. The secondary outcome measures of this study are (1) the between-group differences in changes in the MoCA-K scores 6 weeks after baseline; (2) the between-group differences in changes in the MoCA-K scores 24 weeks after baseline, and (3) the changes in the GDS, Alzheimer’s Disease Assessment Scale-cognitive subscale-3 (ADAS-K-cog 3), and European Quality of Life Five Dimension Five Level scale (EQ-5D-5L) scores 6, 13, and 24 weeks from baseline.

MoCA, a screening instrument that is widely used to detect MCI, is used to measure the changes in cognitive function. It is a 30-point test that can evaluate the cognitive domains of orientation to place and time, visuospatial/executive function, short-term memory recall, concentration, attention, working memory, and language (26, 27).

ADAS-K-cog 3 is used to evaluate memory. It includes three tasks of the ADAS-K-cog 11 (orientation, word recall, and word recognition), which demonstrate no ceiling effects in MCI (28).

GDS is used to identify depression as it can distinguish between the symptoms of depression and dementia in elderly people. This is a widely used screening instrument for evaluating depressive symptoms in elderly individuals (29).

EQ-5D-5L is a commonly used health utility instrument to explore quality of life (30). The quality weight of EQ-5D-5L was based on a previous study (31).

#### Safety outcome

2.13.2

Safety assessments will be conducted by comparing the occurrence of adverse events (AEs) and the changes in pulse rate, blood pressure, and blood chemistry parameters between the two groups.

### Adverse events

2.14

The possible AEs include bleeding, skin irritation, dizziness, pallor, local hematoma, and fainting. The CRC will record AEs occurring during the trial period, including the severity, date and time of occurrence, treatment process, and relationship between the AE and intervention. All AEs and SAEs will be reported to the PI and IRB and monitored until they stabilize. The participants will be compensated according to the applicable regulations in the event of SAEs and AEs related to our treatment.

### Quality control

2.15

Experts in acupuncture, MCI, statistics, rehabilitation, and methodology developed and reviewed this protocol. All researchers will receive intensive training before commencing the trial to fully understand the protocol and standard operating procedures (SOPs). An independent clinical research associate will evaluate all documents related to this trial and monitor the trial to ensure that this study is conducted according to SOPs and protocols. Any revision of the protocol will be approved by the IRB.

### Sample size estimation

2.16

We adopted sample sizes from a previous study that was similar to our study design and aimed to investigate the efficacy of acupuncture for MCI using the MoCA score as the primary outcome. In that previous study (32), the sample size was calculated assuming an expected curative effect of 90% in the acupuncture group and 67.9% in the control group, a two-sided alpha level of 0.05, and a statistical power of 0.8.

$$n=\frac{8pq}{\left(p1-p2\right)2}$$

In the equation, p1 and p2 represent the original curative effect (the rate of cognitive training) and expected curative effect (the rate of acupuncture treatment) of 67.9 and 90%, respectively. p = $\frac{p1+p2}{2}$ = 0.79, q = $\frac{1-p1+1-p2}{2}$ = 0.21.

The sample size was estimated as 27 participants per group, and assuming a maximum dropout rate of 15%, 64 participants (32 in each group) will be included in the trial.

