### Objective

2.1

We intend to investigate the efficacy of acupuncture for MCI by comparing its effect on cognitive improvement with that of computerized cognitive rehabilitation (CCR).We intend to evaluate the ability of acupuncture to improve the quality of life, memory, and depressive symptoms in patients with MCI.We also intend to explore the safety of acupuncture in patients with MCI.

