A preliminary clinical study was conducted to compare the effects of CCR combined with EA and CCR alone to explore the effects of EA on MCI. EA combined with CCR, which was applied simultaneously with EA at Baihui (GV20), Sishencong (EX-HN1), Fengchi (GB20), and Shenting (GV24) and Rehacom software therapy for 30 min in a sitting position, had no positive add-on effects on the depressive symptoms, quality of life, activity of daily life, and cognitive ability in patients with MCI in the preliminary study (24). This trial has some improvements compared with the preliminary study. First, a larger sample size will be used to explore the effects of acupuncture on MCI. The preliminary study was a pilot study (*n* = 18 in each group), whereas this trial will have a sample size (of 32 in each group) based on that of a previous study. Second, the acupuncture treatment method has been modified based on the results of the preliminary study. Acupoint specificity, psychological factors, and duration of treatment can affect the efficacy of acupuncture. The choice of acupoints plays a crucial role in ensuring the positive therapeutic effects of acupuncture. GV24 (Shenting), EX-HN1 (Sishencong), and GV20 (Baihui), the most commonly used acupoints in previous studies, will also be used in this trial (16, 20). These acupoints are connected to the brain and play important roles in cognition (20). The participants in the preliminary study received EA stimulation at GV24, GV20, EX-HN1, and GB20 in the seated position. However, the participants showed resistance to EA treatment owing to discomfort in the seated position and the large number of EA stimulations. Therefore, in this study, EA will be performed at GV20 (Baihui) and GV24 (Shenting) (23) and acupuncture will be performed at EX-HN1 (Sishencong) in the supine position. Moreover, body acupuncture will not be adopted. MCI is a neurodegenerative disease that progresses slowly; therefore, the treatment duration was changed from 8 weeks to 12 weeks to achieve sufficient therapeutic effects based on the findings of previous studies (21, 32–34). Third, the interventions of the test and control groups were changed from EA combined with CCR and CCR to EA and CCR, respectively, to explore the effects of EA on MCI rather than add-on effects. Previous studies exploring the efficacy of acupuncture for MCI used sham acupuncture, pharmacological intervention, and usual care as interventions in the control group (12, 13, 15, 32–34). Sham acupuncture has been used in clinical studies on acupuncture to exclude the placebo effects. However, recent studies have shown that sham acupuncture should not be considered the same as placebo owing to the unexpected therapeutic effects of sham acupuncture at the same location (35, 36). There are no recommended drugs for MCI with a high level of evidence (9, 10). Therefore, CCR using Rehacom software will be used as the treatment in the control group. CCR may have positive effects on memory, attention, and executive function in patients with MCI (37, 38). As Rehacom provides standard tasks with immediate feedback, it is useful for the treatment of MCI and clinical trials (23). Fourth, the primary efficacy outcome was changed from ADAS-K-cog to the MoCA-K. MoCA has been used as the primary outcome in recent studies exploring the effects of acupuncture on MCI (16, 32, 34, 39). In addition, MoCA has also been used to evaluate early cognitive decline and cognitive reserve (CR). CR, a concept based on brain plasticity, counteracts the effects of brain damage and aging (40). CR has been proposed as a potential protective factor against dementia or MCI (41).

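### The protocol describes the control arm behind the 67.9% rate in two conflicting ways, so the 0.8 power is not shown for the CCR comparator

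*Protocol article*

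**What the plan says.** The objective (2.1) is to judge acupuncture by "comparing its effect on cognitive improvement with that of computerized cognitive rehabilitation (CCR"), and 2.2 expects acupuncture to do better than the control.

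For the size, 2.16 states: "We adopted sample sizes from a previous study that was similar to our study design". That study is reference 32. Its own calculation is reported as "assuming an expected curative effect of 90% in the acupuncture group and 67.9% in the control group", with two-sided alpha 0.05 and power 0.8. Beneath the formula, the two inputs are said to "represent the original curative effect (the rate of cognitive training) and expected curative effect (the rate of acupuncture treatment) of 67.9 and 90%, respectively", so the 67.9% carries the cognitive-training label. The result is 27 per group, raised to 32 per group (64 in total) for 15% dropout.

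The Discussion says that previous acupuncture trials in MCI "used sham acupuncture, pharmacological intervention, and usual care as interventions in the control group (12, 13, 15, 32–34"). Cognitive training is not among the control types listed. After setting aside sham needling and drugs, the text presents CCR with RehaCom as this trial's control and says that "CCR may have positive effects on memory, attention, and executive function in patients with MCI".

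**The concern.** One cited study supplies the control rate that sets n, and the article describes its control in two ways. In 2.16 the rate belongs to cognitive training, which would be close to this trial's comparator. In the Discussion the same reference sits among trials with sham, drug or usual-care controls, from which the present design is said to depart.

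If the Discussion is right about reference 32, the 22.1-point difference (90 − 67.9) is a contrast with some other comparator, carried over to a trial against a treatment that the protocol itself regards as possibly effective. If 2.16 is right, the Discussion misdescribes the study. In both cases a reader cannot tell whether 67.9% is a rate for anything like CCR, and no other section gives a CCR response rate. A non-significant result could then be taken as an adequately powered comparison with CCR when that has not been shown.

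**Working it through.** **The passages side by side.** Section 2.16 speaks of reference 32 individually and ties 67.9% to cognitive training. The Discussion speaks of references 12, 13, 15 and 32–34 together, lists three control types, and does not assign a type to each reference. On a plain reading they conflict. They are not logically incompatible, because a group citation does not exclude a cognitive-training arm in one of the studies.

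**Reproducing the stated size.** The inputs from 2.16 are p1 = 0.679 and p2 = 0.90, so p = 0.7895, q = 0.2105 and p2 − p1 = 0.221.

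n = 8pq/(p1 − p2)² = 8 × 0.7895 × 0.2105 / 0.221² = 27.2, stated as 27. For dropout, 27/0.85 = 31.8, so 32 per group and 64 in total. The printed arithmetic reproduces.

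**Why the printed formula is not used for power here.** At two-sided 0.05 and 80% power, (1.96 + 0.842)² = 7.85, and a difference between two groups needs twice that, 15.7. The printed constant of 8 lacks the factor of 2. That is a separate matter, but it means that power has to come from a standard two-group calculation.

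**Power over a range of CCR rates.** Assumptions: acupuncture stays at 90%, 27 are evaluable per group, and the test is two-sided at 5%. The CCR rate c is varied in both directions because the documents do not establish one. With p = (c + 0.90)/2 and q = 1 − p:

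power = Φ{[(0.90 − c)√27 − 1.96√(2pq)] / √[c(1 − c) + 0.90 × 0.10]}

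At c = 0.679: (0.221 × 5.196 − 1.130)/0.555 = (1.148 − 1.130)/0.555 = 0.033, and Φ(0.033) = 0.513.

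| Assumed CCR rate | Power at 27 per group | n per group for 80% power |
|---|---|---|
| 60% | 73% | 32 |
| 65% | 60% | 43 |
| 67.9% | 51% | 53 |
| 70% | 45% | 62 |
| 75% | 30% | 100 |
| 80% | 17% | 199 |

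Around the stated rate, about 8 points lower (60%) raises power by 22 points, and about 7 points higher (75%) lowers it by 21. The identity of the comparator behind the 67.9% is therefore material whichever way the truth lies.

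**Limit of these figures.** The primary outcome (2.13.1) is a between-group difference in MoCA-K change at 13 weeks, which is continuous. The table shows how the plan's own binary-rate reasoning responds to the control rate. It is not the power of the primary analysis.

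**The case against.** The strongest reply is that no contradiction is proved. The Discussion sentence is a group citation without the word only. A multi-arm study, or usual care that included cognitive training, would satisfy both passages, and 2.16 is the only place that describes reference 32 on its own. A citation slip is also plausible: the Discussion cites reference 21 among studies supporting the treatment duration, whereas 2.3 cites it for the SPIRIT checklist. This stands. A reader might infer that 67.9% is certainly not a cognitive-training rate, and the documents do not support that.

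A reader might also infer that CCR must exceed 67.9% and that the transfer therefore overstates power. Nothing in the documents fixes the direction. Nor does the preliminary study (18 per group): it tested electroacupuncture added to CCR, found no add-on benefit, and does not estimate acupuncture against CCR.

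Third, the borrowing is disclosed, and the 0.8 is worded as an assumption of the earlier study. That is correct. But 2.16 gives no other justification of size, calls the earlier design similar and attaches the cognitive-training label, so readers will carry the 0.8 over to this trial.

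Finally, the formula's constant and the use of a binary rate for a continuous outcome are larger sizing problems, and settling the label cures neither. This is also true. It limits the weight of the present point without removing it, because a corrected formula would still need to know whose rate the 67.9% is.

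**Conclusion.** The point holds in a limited form. The article leaves open whether the 67.9% comes from a cognitive-training control, so 0.8 is not shown as the power against CCR. On a standard two-group calculation with acupuncture at 90% and 27 evaluable per group, binary-rate power is about 51% even at the stated 67.9%, and runs from 73% to 17% as the assumed CCR rate goes from 60% to 80%. The shortfall at 67.9% itself comes from the formula's constant and not from the comparator. The comparator question determines where in that range the trial sits, and the documents cannot answer it.

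The documents do not show that the trial was sized on the wrong comparator. Nor do they plan to read a non-significant result as equivalence: the stated hypothesis is superiority.

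**What to change.** 1. Check which arm of reference 32 produced the 67.9%, then correct either the label in 2.16 or the Discussion citation so that the two agree. If the control was not cognitive training, withdraw the label and qualify the claim of a similar design.
2. Say in 2.16 that n = 64 and the 0.8 power are borrowed from that study and are not the power of this trial against CCR.
3. Report power over CCR rates on both sides of 67.9%, for example 60% to 80%, from a standard two-group calculation with the assumptions stated, and note that these binary-rate figures are not the power for MoCA-K change.

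The cost is one source check, some wording in 2.16 and possibly one Discussion sentence. The sample size stays at 64, with no added patients and no change to the analysis. The downside is a less favourable stated power.

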### Statistical analysis

2.17

An independent statistician will analyze the final data using SPSS software (version 21.0, IBM). A full analysis set will be conducted to assess the efficacy of the treatment, and missing data will be inputted using the last observation carried forward method. The significance level will be set at 5% (two-tailed). Categorical variables will be expressed as percentages or frequencies, whereas continuous variables will be expressed as mean and standard deviation or median with an interquartile range. Interim analysis will not be performed.

Friedman test or a one-way repeated-measures analysis of variance for intragroup comparisons and analysis of covariance, as well as an independent *t*-test or Mann–Whitney U test will be used for intergroup comparisons to analyze the changes in efficacy outcomes. Sub-analyses will be conducted according to age (under 70 and over 70 years old).

The occurrence of AEs between the two groups will be compared using the chi-square test or Fisher’s exact test. The Mann–Whitney U test or independent *t*-test will be used for intergroup comparisons to analyze the changes in blood chemistry parameters, blood pressure, and pulse rate.

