**Methods:**

The trial will be a randomized, prospective, parallel-arm, active-controlled trial. Sixty-four patients with MCI will be randomized to the Rehacom or acupuncture group (*n* = 32 each). The participants in the acupuncture group will receive electroacupuncture at GV24 (Shenting) and GV20 (Baihui) and acupuncture at EX-HN1 (Sishencong) once (30 min) a day, twice per week for 12 weeks. The patients in the Rehacom group will receive computerized cognitive rehabilitation using RehaCom software once (30 min) daily, twice weekly for 12 weeks. The primary outcome measure is the change in the Montreal Cognitive Assessment Scale score. The secondary outcome measures are the Geriatric Depression Scale, Alzheimer’s Disease Assessment Scale-Korean version-cognitive subscale-3 scores, and European Quality of Life Five Dimensions Five Level Scale. The safety outcomes will include the incidence of adverse events, blood pressure, blood chemistry parameters, and pulse rate. The efficacy outcome will be assessed at baseline and at six weeks, 13 weeks, and 24 weeks after baseline.

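### Last observation carried forward is the only stated handling of missing efficacy scores; it can bias the week-13 and week-24 comparisons and overstates the information collected

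*Protocol article*

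**What the plan says.** Protocol article, section 2.17 (Statistical analysis), on gaps in the efficacy scores: "missing data will be inputted using the last observation carried forward method". This applies within the full analysis set, which the same sentence names for the efficacy analysis. No other method for missing scores is named. The per-protocol exclusions in section 2.7 concern protocol violations and attendance, not missing scores.

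Section 2.13.1 (Efficacy outcome): "The primary outcome measure is the between-group difference in changes in MoCA-K scores 13 weeks after baseline". Secondary outcomes include "the between-group differences in changes in the MoCA-K scores 24 weeks after baseline".

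Abstract, Methods: "The efficacy outcome will be assessed at baseline and at six weeks, 13 weeks, and 24 weeks after baseline". Baseline and week 6 are therefore the only scores that can be carried into week 13.

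Section 2.16 (Sample size estimation) expects some loss: "assuming a maximum dropout rate of 15%, 64 participants (32 in each group) will be included in the trial". Section 2.7 makes any serious adverse event a ground for dropout, and section 2.10 states blinding for statisticians, assessors and data analysts only.

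**The concern.** Carrying a score forward assumes that it would not have changed after the last visit. The trial is built on the opposite expectation. It hypothesises improvement under treatment, and the Discussion explains that treatment was lengthened from 8 to 12 weeks so that an effect has time to develop. Scores are thus expected to move after week 6.

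Three things are at stake:

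- **Primary comparison.** A carried baseline or week-6 score enters week 13 as if it had been measured there. If loss differs between arms in amount or timing, the arms are shifted by different amounts.
- **Week 24.** A participant lost after week 13 is given the end-of-treatment score, so any later change in that person, up or down, cannot appear.
- **Precision.** Filled-in scores count as observations, so the standard error reflects more information than was collected.

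The carried values also enter the planned within-group repeated-measures or Friedman tests as repeat measurements.

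**Working it through.** **Inputs from the protocol article.** 32 per arm; up to 15% dropout (section 2.16); efficacy scores at baseline and weeks 6, 13 and 24.

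**The plan's own figure.** 27 / 0.85 = 31.8, rounded up to 32 per arm, so the stated allowance reproduces. It means about 0.15 × 32 = 4.8, or 5 participants per arm. The sample size treats these participants as lost, whereas section 2.17 fills in their scores.

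**Assumed, because the documents do not give them.** Mean MoCA-K changes, SD, correlation, and dropout by arm and by time. In the week-13 cases loss is split evenly between before week 6 and weeks 6 to 13, and everyone lost stays in the full analysis set.

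**Formula, week 13.** Let c6 and c13 be the mean changes in an arm, d6 the fraction lost before week 6 and d13 the fraction lost between weeks 6 and 13. The arm's expected mean is

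(1 − d6 − d13) × c13 + d13 × c6 + d6 × 0.

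**Case 1: no true difference.** Both arms gain 1.5 at week 6 and 2.5 at week 13.
- 5% lost: 0.95 × 2.5 + 0.025 × 1.5 = 2.4125
- 15% lost: 0.85 × 2.5 + 0.075 × 1.5 = 2.2375
- 25% lost: 0.75 × 2.5 + 0.125 × 1.5 = 2.0625

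False difference against the arm with more loss: 0.175 for 15% versus 5%, and 0.35 for 25% versus 5%. With equal loss it is 0.

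**Case 2: true week-13 difference of 1.0 (0.5 at week 6), equal loss.**
- 15% lost by week 13 in each arm: 0.85 × 1.0 + 0.075 × 0.5 = 0.8875
- 10% lost by week 13 in each arm: 0.90 × 1.0 + 0.05 × 0.5 = 0.925

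**Case 3: week 24.** Both arms fade from 2.5 at week 13 to 1.0 at week 24, and all loss is after week 13.
- 20% lost: 0.80 × 1.0 + 0.20 × 2.5 = 1.30
- 5% lost: 0.95 × 1.0 + 0.05 × 2.5 = 1.075

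False difference: 0.225, in favour of the arm with more loss.

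**Precision and coverage.** 20,000 simulated trials per scenario: 32 per arm, t-test on change, SD 3, correlation 0.6 between visits, half of the week-13 change reached by week 6, half of the loss before week 6, loss completely at random.

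| Loss, acupuncture / control | Mean change | True difference | LOCF estimate | 95% CI coverage |
|---|---|---|---|---|
| 15% / 15% | 2 / 2 | 0 | 0.00 | 94.8% (type I error 5.2%) |
| 25% / 5% | 2 / 2 | 0 | −0.30 | 92.2% (type I error 7.8%) |
| 5% / 25% | 2 / 2 | 0 | +0.30 | 92.5% (type I error 7.5%) |
| 15% / 15% | 3.5 / 2 | 1.5 | 1.33 | 94.3% |
| 25% / 5% | 3.5 / 2 | 1.5 | 0.92 | 86.3% |
| 5% / 25% | 3.5 / 2 | 1.5 | 1.75 | 93.4% |

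In the first row the mean reported standard error is 0.658, against 0.725 from participants actually measured at week 13: 0.658 / 0.725 = 0.908, about 9% smaller. The sampling SD of the LOCF estimate itself is 0.662.

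**The case against.** Several stronger readings are tempting, and the documents do not support them.

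- **That the comparison is necessarily biased.** It is not. With equal loss and equal change the between-group bias is zero, and otherwise its direction is unknown in advance.
- **That dropouts are always frozen at an unchanged score.** This is true only of loss before week 6. Later losses carry a partial or full treatment change.
- **That the confidence intervals are generally too narrow.** The reported standard error (0.658) nearly equals the estimate's own sampling SD (0.662), so the coverage lost in the simulation comes mainly from bias. The understatement is relative to the information observed.
- **That durability at week 24 will be overstated.** This needs scores to fade after treatment, which the documents do not predict.
- **That the pilot shows unequal loss is coming.** The Discussion reports resistance to electroacupuncture but attributes it to the seated position and the number of stimulations, and both were changed. Visits may also be rescheduled to support attendance. Unequal loss remains possible, because participants are not stated to be blinded and the interventions differ visibly.
- **That natural decline alone rules out a constant score.** The article says "MCI is a neurodegenerative disease that progresses slowly", and its Introduction allows that cognition may stabilise or return to normal. Over these few months that is weak evidence; expected treatment change is the better argument.

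Two more points stand. A loss of 25% in one arm exceeds the planned 15% if that figure caps each arm, which is why the 15% versus 5% case is shown. And the article does not define the full analysis set, which a full protocol may do. If participants with no score after baseline were excluded, Case 1 would fall to 2.4125 / 0.975 − 2.2375 / 0.925 = 2.474 − 2.419 = 0.06, or to 2.474 − 2.0625 / 0.875 = 0.12 for 25% versus 5%. That is smaller, but not zero.

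The absence of stated sensitivity analyses is not held against an article that condenses a fuller document.

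**Conclusion.** The concern holds in conditional form. LOCF is a rule that section 2.17 fixes, not a detail left open. Followed as written, it can bias the week-13 and week-24 comparisons in either direction when loss differs between arms. It also dilutes a true difference that is still growing after the last observed visit, even with equal loss.

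Under the assumed values the false week-13 difference is 0.18 to 0.35 point, a true 1.0-point difference shrinks to 0.89 to 0.93, and the false week-24 difference is 0.23 point. The standard error is about 9% too small for the information observed in the one scenario examined. All of these depend on assumed changes, SD, correlation and dropout patterns, and on keeping early losses in the analysis set. This should be changed, because a less bias-prone method is available at little cost.

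**What to change.** In section 2.17, replace LOCF as the primary method with a likelihood-based mixed model for repeated measures on the observed MoCA-K scores at weeks 6, 13 and 24. Include arm by visit and baseline by visit terms and an unstructured covariance, and name the week-13 arm contrast as the primary analysis. The week-6 and week-24 contrasts come from the same model, and the other efficacy scales can be handled in the same way. Multiple imputation under missing at random is an acceptable alternative. Keep LOCF at most as a sensitivity analysis.

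The cost is revised wording and a little more analysis work. No new visits or data are needed, and the MIXED procedure in SPSS, the software already named, can fit the model. The downside is reliance on missing at random, which a delta-adjusted sensitivity analysis can probe.

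### The plan applies ANCOVA and an unadjusted test to the same primary comparison and does not say which one decides

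*Protocol article*

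**What the plan says.** Section 2.13.1 (Efficacy outcome) defines a single primary endpoint at a single time: "The primary outcome measure is the between-group difference in changes in MoCA-K scores 13 weeks after baseline".

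Section 2.17 (Statistical analysis) has one sentence on how efficacy is tested. It gives the Friedman test or repeated-measures ANOVA "for intragroup comparisons and analysis of covariance", "as well as an independent *t*-test or Mann–Whitney U test will be used for intergroup comparisons", all "to analyze the changes in efficacy outcomes". ANCOVA is a between-group method, so the natural reading puts it with the t-test or Mann–Whitney test on the between-group side. The same section sets significance at two-sided 5%, uses the full analysis set and excludes an interim analysis.

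The sentence covers every efficacy outcome. It reaches the primary endpoint because no other section gives that endpoint its own rule. The ANCOVA covariate is not named, nor is the condition for choosing the t-test or the Mann–Whitney test.

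**The concern.** The wording joins ANCOVA and the unadjusted test additively. It does not offer them as alternatives. The primary hypothesis in section 2.2, that acupuncture improves cognition more than computerised rehabilitation, is therefore tested at least twice at the full 5%, with no stated order of precedence.

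Two things are at stake. First, if either result may be presented as the primary one, the false-positive rate exceeds the nominal level. Second, the two tests can disagree when there is a real effect, and a reader of the published plan could not then tell whether the trial had met its objective. The unadjusted tests on change are also usually the less precise choice, which matters with 64 participants.

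**Working it through.** **Inputs.** From section 2.16: "The sample size was estimated as 27 participants per group", raised to 32 for 15% dropout, with "a two-sided alpha level of 0.05, and a statistical power of 0.8". The stated formula reproduces these numbers: 8 × 0.79 × 0.21 / (0.90 − 0.679)² = 1.3272 / 0.048841 = 27.2, taken as 27; and 27 / 0.85 = 31.8, taken as 32. They serve here only as arm sizes for the simulation. Whether the formula suits the trial is a separate question.

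**Assumption.** The sample size rests on response rates, so the article gives no standard deviation for MoCA-K and no correlation *r* between baseline and 13 weeks. I take *r* = 0.4–0.7 as the main range and show 0.3 and 0.8 as extremes.

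**Step 1: type I error.** The simulation used 20,000 trials per setting, bivariate normal scores with equal variances and no treatment effect. It compared ANCOVA adjusted for baseline with the t-test and Mann–Whitney test on change. Percentage of trials with p < 0.05, at 27 / 32 per arm:

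| *r* | ANCOVA alone | t-test alone | ANCOVA or t-test | Any of the three |
|---|---|---|---|---|
| 0.3 | 4.95 / 5.00 | 5.19 / 5.04 | 7.84 / 7.80 | 8.60 / 8.55 |
| 0.5 | 4.96 / 4.92 | 4.86 / 5.08 | 7.21 / 7.42 | 7.87 / 8.20 |
| 0.7 | 4.80 / 4.95 | 4.82 / 4.86 | 6.66 / 6.71 | 7.24 / 7.32 |
| 0.8 | 5.06 / 5.24 | 5.06 / 5.26 | 6.54 / 6.72 | 7.24 / 7.44 |

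Each test alone holds about 5%. Allowing either of two gives about 6.5–8%. Running all three gives up to about 8.5%. If the unadjusted test is instead picked by a Shapiro–Wilk test (an assumption; the article states no rule), ANCOVA plus the chosen test gives 6.7–7.4% at 27 per arm and 7.0–7.9% at 32.

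**Step 2: disagreement under a real effect.** With the effect set so that the t-test on change has about 77–80% power, and *r* = 0.4–0.7, ANCOVA has about 83–91% power. The two tests disagree on significance in about 9–14% of trials (up to 15% in one run). With the effect set so that ANCOVA has about 78% power, at 27 per arm:

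| *r* | ANCOVA | t-test | Mann–Whitney | ANCOVA and t-test disagree |
|---|---|---|---|---|
| 0.5 | 77.8% | 66.2% | 62.9% | 17.0% |
| 0.7 | 77.6% | 71.7% | 69.0% | 11.3% |

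**Step 3: precision.** With equal variances σ², the variance of change is 2σ²(1 − *r*) and the ANCOVA residual variance is σ²(1 − *r*²). The ratio of ANCOVA to change is (1 − *r*²) / [2(1 − *r*)] = (1 + *r*)/2. That is 0.70 at *r* = 0.4, 0.75 at 0.5 and 0.85 at 0.7.

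**Step 4: effect of the entry limit.** Section 2.5 admits only MoCA-K 0–22, which may shrink the baseline variance to a fraction *v* of its unrestricted value. The ratio then becomes (1 − *r*²) / [(1 − *r*²) + (1 − *r*)²*v*]. Truncation at the 70th percentile (assumed) gives *v* ≈ 0.49; with *r* = 0.5 the ratio is 0.75 / (0.75 + 0.25 × 0.49) = 0.86. Truncation at the 30th percentile gives *v* ≈ 0.26; with *r* = 0.7 the ratio is 0.51 / (0.51 + 0.09 × 0.26) = 0.96. The gain then falls to about 4–14%. Table 1 schedules MoCA-K at screening and again at allocation. If the allocation score is the analysis baseline, truncation is only partial and the gain lies between the two cases.

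**The case against.** The strongest reply is that this is a condensed article, and that covariates, the rule for parametric or rank tests and the label of the deciding model are commonly left to an analysis plan. The endpoint, time point, analysis set and alpha are fixed. Section 2.10 blinds the statisticians and data analysts, and section 2.17 gives the analysis to an independent statistician. ANCOVA is already listed, and a t-test on change is valid at 5% in a randomised trial.

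Much of this stands. The unnamed covariate and the missing rule for t-test or Mann–Whitney would not be findings by themselves. Blinding limits selective reporting, although it does not say which result counts. What remains is that the article does state the analysis, and what it states is two tests of one quantity without an order.

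A reader might infer more than the text supports:

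- **Three p-values for the primary endpoint.** The text offers the t-test or the Mann–Whitney test, so two is the literal count and three the upper case.
- **Selection by a normality test.** This is plausible, but no such rule is stated.
- **Simple randomisation that leaves chance imbalance uncorrected.** Section 2.8 mentions only random numbers from SPSS and 32 per arm. The method is not given.
- **The weaker test will decide, or the favourable result will be chosen.** Nothing says so. The text merely does not prevent it. Nor is Mann–Whitney always weaker: with heavy-tailed data it can gain power.

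**Conclusion.** The point holds as a missing order of precedence between two stated tests of the primary endpoint. It should be fixed, but it does not invalidate the design.

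The inflation, to about 6.5–8%, is modest because the tests are correlated, and it arises only if either result may count as primary. The disagreement rate of about 9–14% depends on the assumed effect and on *r* = 0.4–0.7. The precision advantage of ANCOVA assumes baseline MoCA-K as covariate and roughly normal data. Its size is uncertain: 15–30% lower variance at *r* = 0.7–0.4 with equal variances, and perhaps only 4–14% if the entry limit truncates baseline. The absence of a stated deciding test is certain from the text. The magnitudes are conditional on these assumptions.

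**What to change.** In section 2.17, name one primary analysis: MoCA-K at 13 weeks compared between arms by ANCOVA adjusted for pre-randomisation MoCA-K, at two-sided 5%, reported as the adjusted difference with its 95% CI. Because Table 1 has two early MoCA-K assessments, say which one is the covariate. Label the t-test or Mann–Whitney test on change as supportive, with no role in deciding the primary hypothesis.

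The cost is about one sentence, agreed before unblinding. Baseline MoCA-K, ANCOVA and SPSS are already in the plan, so no new data, participants or software are needed, and the downside is negligible.
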